**Figure 1 fig1:**
[figure not shown]
Study sampling plan.

### Informed consent and client involvement

Clients will be signing the printed informed consent and will be involved in the design and conduct of the study. An orientation will be conducted to communicate the research objectives, outcome measures, recruitment methods, and other relevant information. Client experience and preferences will be identified and incorporated.

## Interventions

This study will involve the development of mixed reality technology-driven virtual coach exercise program. The program shall be called “Hataw at Sigla para kay Lolo and Lola” (Groove and Move for older Adults), and will consist of the following procedures:

*Identifying the standard exercise for Filipino older adults*: the Philippines, similar to other territories, recommend a multimodal exercise as the most ideal program to support and improve the health of older adults (15, 64). This multimodal approach consists of aerobic, resistance, balance, and flexibility maneuvers (16). Developing the exercise program considers the uniqueness of the older adult cohorts with specific needs and requirements and compliance with recommended well-balanced exercise regimens (16). Results of systematic reviews (65, 66) and international expert consensus (64) shall serve as references for the age-appropriate program. The summary of the exercise components and recommendations are presented (Table 1; Figure 2). The ideal duration of the program is 1 h with 15 min of warming up and stretching before and after the session. This session length concurs with the current local recommendations (67, 68).*HT programming*: this study will use a virtual humanoid “digital coach” to be projected using an optical see-through head-mounted-display (OST-HMD), Microsoft^®^ Hololens (see Figure 3). The device has been the most dominant, popular, and fastest developing mixed reality display in healthcare research since its release in 2016 (52, 69) due to its commendable inbuilt processing units and more extensive network of developers in healthcare (70). The device has been used for health and education programs for older adults in previous studies. The Mixed Reality Toolkit version 2, Unity 2018.4.x, and Unreal Engine are the primary software to be used.

**Table 1 tab1:** Summary of best practice recommendations for HEPA program for older adults.

Physical function	Exercise type	Recommendations	HT-HEPA^c^
Strength	Resistance/ Strength	Frequency: 2–3 times per week Volume: 1–3 sets of 8–12 repetitions, 8–10 muscle groups Intensity: start at 30–40 1RM and progress to 70–80% 1RM (Borg Scale = 15–18)^b^	Calisthenics: 1 set of 8–12 repetitions
Agility/ Balance	Balance	Frequency: 2–3 times per week; 90 min per week Volume: 1–2 sets of 4–10 different exercises with emphasis on static and dynamic posture Intensity: light to a moderate intensity as tolerated	Tai-chi, Walking exercise variations: 30 min of balance activity
	Flexibility	2–3 times per week	Stretching: Two sets of 15 min-stretching before and after HEPA sessions
Endurance	Aerobic	Frequency: 2–7 times per week; 150 min per week Volume: 20–60 min per session Intensity: moderate intensity (5-6)^a^ or 75 min per week of vigorous activity (7-8)^a^	Dancing: 1 set of 30-min dancing

a Scale of 0–10, where 0 is the level of effort for sitting, 10 is maximal effort, 5–6 is moderate, and 7–8 is vigorous.

b Original borg scale of perceived exertion from 6 (easy) to 20 (maximal).

c Two sessions per week scheduled every Tuesday and Thursday for the first 2 weeks, and three sessions per week scheduled every Monday, Wednesday, and Friday on the second 2 weeks.

**Figure 2 fig2:**
[figure not shown]
Summary of best practice recommendations for HEPA program for older adults.

**Figure 3 fig3:**
[figure not shown]
Concept diagram of virtual coach projected via see-through head-mounted-display.

### Improving client adherence and post-trial care

The participants (experimental and control) will receive an honorarium for their participation in the study. Other benefits include on-site snacks, free consultation from healthcare providers, and access to wellness facilities where the intervention will be conducted. In addition, participants who will be completing the whole program will receive wellness and exercise program paraphernalia.

### Outcomes

The predictor, outcome, and related variables will be assessed using appropriate, valid, and reliable measurement tools as shown in Table 2.

**Table 2 tab2:** Tools, instruments, and measurements.

Variables/ Measures	Materials and instruments	Properties
Intervention (X)		
	Virtual HT: Hololens^®^ 2 (Microsoft Corp.); Mixed reality devices	Most promising optical see-through mounted display due to its technical possibilities for tracking, interaction, and display (71)
	Adaptive conjoint survey	Practical and respondent-friendly (51)
System usability	Post study system usability questionnaire	Reliable (0.94), valid, adaptable, and practical (72)
Technology acceptance	Universal theory of acceptance and use of technology (UTAUT) questionnaire	Construct ICRS greater than 0.70, valid and reliable (73)
Outcome (Y)		
Physical		
Physical status	6-min walk test	Interclass reliability ICC = 0.94 (74)
Cognitive		
Cognitive status	Montreal cognitive assessment (MoCA)	Test–retest reliability between 7.1 and 7.2 (ICC: 0.64), and excellent between 7.1 and 7.3 (ICC: 0.82) (75)
Quality of life		
HRQoL	SF-8 quality of life (QoL)	TRR = 0.73, 0.74; α = 0.92 (76, 77)
Others (Z)		
Demographics, literacy	Residence, gender, age, marital status, education, technology literacy	Socio-demographic determinants linked to promoting health (78)
Health behavior	Patient action inventory for self-care	α = 0.95, 0.97, 0.97 (79)
Geriatric depression	Geriatric depression scale	IC (α = 0.92); SE (0.92); SP (0.91); PPV (76%); NPV (0.97) (80)
Anxiety symptoms	Spielberger state–trait inventory (STAI)	ICC =0.82–0.95 (81)
Sleep quality	Pittsburg sleep quality index	SE = 0.90; SP = 0.87 (82)

### Data collection and timeline

This study is composed of three data collection steps:

*Step 1: preparatory*: this phase includes the necessary preparation to enrich the effectiveness and efficiency of data collection through (1) an initial visit to the senior center sites to establish a partnership with the administration, orientation, acquire permission, and establish rapport among the prospective subjects, (2) technical set-up and training, and (3) health screening and actual sampling.*Step 2: quantitative evaluation of preferences*: this phase involves the initial assessment of the older adults’ preferences for the mixed reality technology-driven exercise program via conjoint analysis. Results will be generated to inform the mixed reality technology system programming for the system’s actual development and initial pilot. This will follow the baseline assessment of participant data, actual exposure to the intervention, and post-intervention assessment of the subjects. The intervention will run for a month consisting of the first 2 weeks of the twice-weekly (Tuesday and Thursday) schedule to be followed by the second 2 weeks of trice weekly (Monday, Wednesday, Friday) schedule. Each intervention session program will last approximately 1.5 h, including orientation, warm-up, and stretching. All participants will be supervised by the health team and trained personnel at the senior center and follow a standard protocol.*Step 3: qualitative evaluation*: this phase focuses on the individual interviews to assess views and opinions of study participants. An *aide-memoire* will be constructed as an interview tool to capture the stories and experiences of the older adult participants. Specifically, a responsive interviewing approach (83) will be used. Individual interviews will be transcribed, coded, and thematized. Qualitative findings will be used to substantiate the quantitative outcomes of the study.

### Sample size

To identify the acceptable sample size, the difference in repeated measures between two independent groups using MANOVA with a power set at 0.80 with medium to high effect size at 0.05 alpha level was computed using R software. The estimated sample size is 128 or 64 participants per senior center group.

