## Objectives

In response to the current gray spots and gaps found in a recently published literature review (31), this study envisions to advance the science of mixed reality technology-driven health interventions in the field of nursing by examining its impact through an exercise program directed toward community-dwelling older adults. Specifically, it aims to:

*Quantitative aim 1*: to assess older adults’ preferences for an ideal mixed-reality-driven virtual coach program based on several attributes and levels. The subjects are hypothesized to select age and ability-specific choices based on previous exposure to technology and life experiences.*Quantitative aim 2*: to evaluate the impact of the mixed-reality-driven virtual coach program on participants’ health. The causal relationship between the outcome variables will be obtained from valid and reliable tools. Older adults with active participation in the program groups are hypothesized to elicit comparable physical and cognitive performances.*Quantitative aim 3*: to model the older adults’ perception of the mixed-reality-driven virtual coach program usability and predictors of intention to participate in the program. The subjects are postulated to show indications of higher behavioral intention to participate in the program as affected by various variables.*Qualitative aim 1*: to understand the older adult participants’ experiences during the mixed-reality-driven virtual coach program. A narrative descriptive qualitative approach will be carried out to evaluate the challenges or difficulties and successes or benefits of the program among those who benefitted the least and most from the intervention. The older adult key informants are expected to story-tell their practices focusing on themes related to acceptability, barriers, and facilitators.

Overall, tt was hypothesized that: (a) the older adult participants will identify their technology preferences based on their previous experiences and combination of various attributes, and (b) the use of mixed reality technology in physical exercise program will produce comparable health assessments when compared with the traditional form of health enhancing physical activities.

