### Study setting, subject, and eligibility criteria

The study will be conducted at two senior centers in urban settings in the Philippines. The senior centers are served by a university-based medical facility located in the northern (Valenzuela City) and southern part (Quezon City) of Luzon Island in the Philippines, where the highest densities of older adults are found.

The eligible participants will be purposively selected from the regular attendees at the study sites using the inclusion criteria: (1) ambulatory, (2) can follow simple instructions, (3) normal eyes functioning without low vision (or at most with corrective lenses), and (4) willingness to participate in the program with signed informed consent. Older adults ages 60–75 regardless of the gender and who are considered fit to participate by the community physician will be targeted. A total of 128 or 64 older adults in each center, will be recruited via posters at community senior centers who will undergo additional screening or health records review by a certified gerontologist to ensure safety and proper fit. Afterward, the treatments will be assigned to each of the two senior center sites for the quasi-experimental study. Only the participants from the experimental group shall be involved in the usability evaluations and qualitative arm. The sampling plan is shown in Figure 1.

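### The 128 people recruited equal the 128 calculated for power 0.80, with nothing allowed for loss, and the named RM-ANOVA by default drops anyone who misses an assessment

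*Protocol article*

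**What the plan says.** The Sample size section of the protocol article bases its calculation on "the difference in repeated measures between two independent groups using MANOVA", sets power at 0.80, and describes the target only as a "medium to high effect size" with alpha 0.05. It concludes: "The estimated sample size is 128 or 64 participants per senior center group". It gives no numeric effect size, number of measurements, correlation or loss rate.

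The Abstract and the section Study setting, subject, and eligibility criteria use the same 128 (64 per centre) as the recruitment figure. These people "will be recruited via posters at community senior centers who will undergo additional screening or health records review by a certified gerontologist". The preparatory step under Data collection and timeline names health screening before sampling in a single item, so the order of the two is not settled.

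The section on repeated measures analysis of variance fixes the analysis of the health outcomes: RM-ANOVA in SPSS 22 over three assessment points, with Mauchly's test and the Greenhouse-Geisser correction. Nothing is said there about incomplete participants.

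Two other passages bear on the point. Under Improving client adherence and post-trial care, "participants who will be completing the whole program will receive wellness and exercise program paraphernalia". Under Objectives, Quantitative aim 2 reads: "Older adults with active participation in the program groups are hypothesized to elicit comparable physical and cognitive performances".

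**The concern.** A sample size calculation returns the number that must be analysed. Here that number is also the number recruited, so every person lost comes straight off the calculated size. The named analysis makes this worse. The usual SPSS repeated-measures procedure needs a full set of assessments from each person, so a participant with two of three values contributes nothing to that outcome.

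Two things are at stake. The first is power: the study expects comparable results in the two groups, and in an underpowered comparison a non-significant difference is easily read as support for that expectation. The second is who remains. One centre receives the head-mounted display programme and the other live coaching with video. People may miss assessments for different reasons in each, so the complete cases need not be alike.

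**Working it through.** **Inputs.** From the Sample size section: alpha 0.05, power 0.80, two groups of 64. Assumed, because the article does not say: a two-sided test, a standardised difference d = 0.5 (the conventional medium value), and losses of 5 to 20%.

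**Reproducing 128.** For a two-sample t test with n per group, the degrees of freedom are 2n − 2 and the noncentrality is d × √(n/2).

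- n = 64: 0.5 × √32 = 2.828 on 126 degrees of freedom; power 0.801.
- n = 63: power 0.795.

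So 64 per group is the smallest number that reaches 0.80 at d = 0.5, and 128 on this reading holds no reserve.

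**Power after loss at d = 0.5.** Remaining n is 64 × (1 − loss), rounded down.

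| Assumed loss | n per group | Noncentrality | Power |
|---|---|---|---|
| 0% | 64 | 2.828 | 0.801 |
| 5% | 60 | 2.739 | 0.775 |
| 10% | 57 | 2.669 | 0.754 |
| 15% | 54 | 2.598 | 0.731 |
| 20% | 51 | 2.525 | 0.706 |

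**Other effect sizes.** The wording of the article also admits effects above medium.

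| d | n per group for 0.80 | Power at 64 | Power at 51 (20% loss) |
|---|---|---|---|
| 0.5 | 64 | 0.801 | 0.706 |
| 0.6 | 45 | 0.920 | 0.851 |
| 0.8 | 26 | 0.994 | 0.979 |

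**Other models.** With f = 0.25 and the average of three measurements correlated 0.5, the total needed is 86; power is 0.930 at 128 and 0.865 after 20% loss. A repeated-measures MANOVA with effect f(V) = 0.25 needs 128 with two measurements and 158 with three.

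**Missed visits under complete-case deletion.** Suppose baseline is complete and each of two later assessments is missed independently by 10% of people (assumed). The complete fraction is 0.9 × 0.9 = 0.81, so 19% of people drop out of the analysis although only 10% are absent at either visit.

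**The case against.** **A larger effect, or the gain from repeated measures, would keep power above 0.80 after loss.** The tables confirm this arithmetic. But under those inputs the calculation would have returned fewer than 128: 90 in total at d = 0.6, 52 at d = 0.8, 86 for the three-measurement average. The article presents 128 as what 0.80 requires. Under whatever inputs gave that answer, loss beyond rounding takes power below 0.80. What stands is that the amount of the shortfall depends on unstated inputs.

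**Missing-data rules belong in an analysis plan that is not shown.** The absence of a rule is indeed no finding. The article does, however, commit to a method and a software package, and the deletion follows from that choice by default. A rule elsewhere could override it, so the complete-case consequence is conditional.

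**The 128 may already be the screened sample.** This is a fair reading. A reader might infer from the eligibility section that screening failures will cut into the 128. The preparatory step allows screening to come first, so that inference is not secure. Later loss is not allowed for on either reading.

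**The completion gift shows little.** It is a retention measure. It suggests that non-completion is thought possible, but not how common it will be, and leaving the programme is not the same as missing an assessment. The intervention is also short, one month, and supervised.

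**Active participation is not an analysis set.** A reader might infer from aim 2 that inactive people will be excluded. The statistical section restricts nobody, and the overall hypothesis at the end of Objectives does not repeat the phrase.

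**Conclusion.** The point holds, conditional on loss. The recruited and calculated numbers are identical, no loss is allowed for, and the named analysis by default discards partly observed participants. If people are lost, the stated 0.80 is not kept. At the assumed d = 0.5 the cost is about 5 percentage points of power at 10% loss and about 10 at 20%. Both d = 0.5 and the loss rates are assumptions.

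Two stronger readings are not supported. The first is that selective loss would push the results toward comparable. Selective loss in one centre could equally make that centre look better, and the documents do not allow the direction to be known. The second is to quote the three-measurement MANOVA figures (0.676, 0.651, 0.625 and 0.598 at 5, 10, 15 and 20% loss) as the effect of attrition. That model gives only 0.706 at the full 128. The step from 0.801 to 0.706 is a change of model; only the further drop, 0.030 at 5% and 0.108 at 20%, is due to loss.

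**What to change.** 1. Replace RM-ANOVA by a linear mixed model for repeated measures (the MIXED procedure in the same SPSS version). Include everyone enrolled, by assigned centre and regardless of sessions attended, and use all available assessments. Any analysis of active participants is secondary.
2. State whether 128 is the number recruited, enrolled after screening or analysed, and reconcile the eligibility section with the preparatory step under Data collection and timeline.
3. Give the assumed effect size as a number, and report power at the expected loss in place of 0.80. The values above are complete-case t-test figures and should be recomputed for the mixed model. That model recovers partial data, but it cannot replace people with no follow-up at all.

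If 0.80 is to be kept with 128 complete, recruitment would rise to 128 / (1 − loss): 128 / 0.90 = 142.2, so 144 as 72 per centre at 10% loss, or 128 / 0.80 = 160 as 80 per centre at 20%.

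Without the extra recruitment, the cost is revised wording, a little more analysis work and a slightly lower stated power, with no new software.

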## Data collection, management and statistical methods

A robust research data management (84) and analysis plan will be implemented to maintain the privacy, confidentiality, integrity, validity, and reliability of the gathered data in all stages of the data lifecycle (84). Only members of the research group will be given access through a double authentication procedure. The institutions currently utilize the latest Sophos SG series UTM firewall system and the Sophos UTM 9 management system that provides comprehensive gateway protection, including network intrusion prevention management. Backup is done every 7 PM daily, and every server is connected to an uninterruptible power supply. In terms of data analysis, the following approaches shall be used:

### Assessment older adults’ preferences for an ideal mixed reality technology-driven health enhancing physical activity program

Descriptive statistics will be used to describe the respondent demographics. In the conjoint method, regression analysis is adopted to relate the probability of choosing several profiles simultaneously. The regression model assumes that “the probability of choosing one profile is a linear function of the attribute levels in the profile” (85). Sawtooth Software Lighthouse Studio version 9.11 statistical package will be employed to calculate individual preference coefficients (utilities) in each attribute level and attribute importance scores (79, 80). In addition, the primary and joint effects of the preference attributes, average importance, and utility values will also be generated (86). In interpreting and reporting the conjoint outcomes, the ESTIMATE checklist (85) developed by the ISPOR Conjoint Analysis Good Research Practices Task Force shall be used.

### Comparing the effects of the mixed reality technology-driven health enhancing physical activities with the usual health enhancing physical activities (live coach and video-based) on participants’ physical, cognitive status, and quality of life measures

#### Repeated measures analysis of variance (RM-ANOVA)

Repeated Measures Analysis of Variance (RM-ANOVA) will be used to investigate the effects of the type of intervention on health variables across three assessment points using SPSS version 22. Mauchly’s Test will be utilized to verify the sphericity assumption with degrees of freedom correction using the Greenhouse–Geisser method. Effect sizes will also be reported.

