#### Phase 2: impact of mixed-reality-driven virtual coach program on participants’ physical, cognitive status, and QoL

##### Quasi experiment

Quasi experimental research will be employed to estimate the effect and examine the causal relationship between the HT-HEPA intervention and the study respondents’ physical, cognitive status, and QoL. Quasi experiments are appropriate for practical situations and ethical compliance for studies involving vulnerable participants such as older adults (53), and allow scholars to conduct rigorous studies under certain limitations and non-control conditions (54).

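### The centre comparison has a causal aim but is not randomised, and its RM-ANOVA names neither covariates nor the term that carries the inference, although plausible confounders are already collected

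*Protocol article*

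**What the plan says.** All references are to the protocol article.

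- **Aim.** Under Quasi experiment, the study is "to estimate the effect and examine the causal relationship between the HT-HEPA intervention" and participants' physical status, cognitive status and quality of life.
- **Selection.** Under Study setting, subject, and eligibility criteria: "The eligible participants will be purposively selected from the regular attendees at the study sites".
- **Allocation.** The same section says that "the treatments will be assigned to each of the two senior center sites for the quasi-experimental study". There is one centre per treatment and no randomisation.
- **Analysis.** The RM-ANOVA section states the method: "Repeated Measures Analysis of Variance (RM-ANOVA) will be used to investigate the effects of the type of intervention on health variables". The outcomes are to be compared over three visits, with Mauchly's test, the Greenhouse–Geisser correction and effect sizes. No covariate is named, and neither the group term nor the group-by-time term is singled out.
- **Available covariates.** Table 2 (Outcomes) has a block labelled Others (Z). It lists "Residence, gender, age, marital status, education, technology literacy", a self-care inventory, the "Geriatric depression scale", an anxiety inventory and a sleep-quality index. The article gives them no role in the centre comparison. The preference analysis only describes demographics.

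**The concern.** Without randomisation nothing makes the two groups alike, so control of confounding is the central analytic choice for a causal aim. The model as named contains none, although the variables that could supply some are already collected.

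The unnamed target term matters because the two candidates fail differently. The group main effect averages over all visits, baseline included, so it takes in any centre difference present before the programme and dilutes a real effect. The group-by-time term removes differences that are constant over time. It remains exposed to characteristics that alter how much a person changes; education or technology literacy could plausibly do so.

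The bias can go either way. The Objectives hypothesise comparable results in the two groups, so a masked difference would mislead as much as a spurious one.

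**Working it through.** **The plan's own figure.** Sample size gives 128 (64 per centre), power 0.80, alpha 0.05 and a medium to high effect with no number attached. Assuming d = 0.5 and a two-sided test, a two-sample t-test needs 63.8, so 64 per group, with power 0.801. The total is thus reproduced by a plain two-group comparison without covariates.

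**Dilution of the group main effect.** Assume that baseline is one of the three assessment points. (Data collection and timeline describes only a baseline and a post-intervention assessment.) The share of a true effect that the main effect keeps is:
- full effect at both later visits: (0 + 1 + 1)/3 = 2/3
- linear build-up: (0 + 0.5 + 1)/3 = 1/2

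**False positives under no treatment effect.** The documents give no centre differences, so every input except the group size is assumed: 64 per centre, residual SD 1, within-person correlation 0.5, three equally spaced visits, and one covariate with SD 1 that differs by 0.5 SD between centres. There were 3,000 simulated trials per scenario. At a true rate of 5% the simulation error is √(0.05 × 0.95/3000) = 0.4 percentage points.

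*A. Covariate shifts the level only, slope 0.4.* The level bias is 0.5 × 0.4 = 0.20.
- Group main effect: 23%. Check: the variance of a three-visit mean is (1 + 2 × 0.5)/3 + 0.4² = 0.827, the standard error is √(2 × 0.827/64) = 0.161, the noncentrality is 0.20/0.161 = 1.24, and rejection is 23.5%.
- Group-by-time: 5.6%, bias 0.00.

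*B. Covariate also shifts change from first to last visit, slope 0.3.* The bias in change is 0.5 × 0.3 = 0.15.
- Group main effect: 36%, bias 0.28.
- Group-by-time, overall two-degree-of-freedom test: 10.9%, bias in change 0.15.
- Change contrast adjusted for the covariate: 4.3%, bias 0.00.
- Like for like, the unadjusted one-degree-of-freedom change contrast has variance 1 + 0.3² = 1.09, standard error √(2 × 1.09/64) = 0.185, noncentrality 0.81 and rejection 12.7%.

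*C. Unmeasured centre difference in change of 0.3, covariate balanced.*
- Overall group-by-time test: 31%.
- Adjusted change contrast: 39%.
- Baseline-plus-covariate ANCOVA: 49%.
- The bias is 0.30 in all three. The unadjusted one-degree-of-freedom contrast gives 39% (0.30/√(2/64) = 1.70). Adjustment neither helps nor harms here; the step from 31% to 39% comes from the more focused test.

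*D. Unmeasured stable centre difference of 0.3, covariate balanced.*
- Adjusted change contrast: 5.0%, bias 0.00.
- Baseline-plus-covariate ANCOVA: 16.9%, bias 0.15, which is 0.3 × (1 − 0.5).
- In groups that start at different levels, therefore, the two analyses answer different questions.

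**The case against.** The strongest reply is that this is a condensed article. Covariate lists and the exact model term often sit in a full protocol or analysis plan, and neither is shown. The word unadjusted does not appear. Mauchly's test and the Greenhouse–Geisser correction concern only within-subject terms, so the text leans towards group-by-time, where stable centre differences already cancel. The Z variables are not labelled as confounders, and depression, anxiety and sleep may themselves respond to exercise. With one centre per arm, no covariate model can isolate the treatment.

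Much of this stands. A reader might infer that known confounding passes straight into the result. The documents do not support that: they report no centre differences, and in scenario A group-by-time stays near 5%. The 2/3 and 1/2 dilution and the rejection rates of 23% to 36% apply only if the group main effect is the test. A reader might also infer that adjustment would cure the comparison; scenario C shows that it would not.

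What does not stand is that the matter is mere missing detail. The section is specific enough to name the model, the software version, the sphericity test and its correction, and the method named is ANOVA, not ANCOVA. Followed as written for a non-randomised causal comparison, it leaves measured imbalance in. That depression, anxiety and sleep may respond to exercise is a reason to use their baseline values only, not to ignore them.

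**Conclusion.** The point holds in a limited form. The stated RM-ANOVA names no covariate and no target term for a causal comparison of two purposively selected groups, one centre per arm, although plausible individual-level confounders are collected.

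The size depends on the term. For group-by-time, the likelier reading, there is no bias if covariates shift only the level. If they also affect change, the assumed scenario gives a bias of 0.15 SD and about 11% false positives (about 13% for the single change contrast), and adjustment returns this to about 4%, which is nominal within simulation error. For the group main effect, the same assumed imbalance gives 23% to 36%.

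These rates illustrate the mechanism and do not predict this trial, because the imbalance and the slopes are assumed. The plan should be changed, since a better analysis is available from data already collected. Confounding by centre itself will remain whatever model is used.

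**What to change.** 1. State the group-by-time contrast, the difference between groups in change from baseline, as the target.
2. Fit it adjusted for prespecified covariates, using values measured at baseline only: age, gender, education, technology literacy, depression, anxiety and sleep. Enter them with covariate-by-time terms, because covariate main effects alone leave the group-by-time contrast unchanged. Omit residence, which is likely to be nearly the same as centre.
3. Report standardised baseline differences between the centres, and keep the unadjusted RM-ANOVA as a sensitivity analysis.
4. If a baseline-adjusted ANCOVA of the post-programme score is also run, label it a sensitivity analysis with a different estimand, not an equivalent.
5. State that adjustment removes only measured individual-level imbalance, that treatment and centre remain aliased, and that the causal claim is limited accordingly.

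The cost is wording, some extra model terms and a few of the 128 − 2 = 126 between-subject degrees of freedom. The variables are already in Table 2; the plan need only confirm that they are taken before the programme starts.

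### The timeline sets out two assessments but the analysis uses three, and the effect size and number of measurements behind the 128 are not stated

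*Protocol article*

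**What the plan says.** Three places in the protocol article bear on this point.

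- **Data collection and timeline, Step 2.** After the preference survey and system development, the sequence is: "This will follow the baseline assessment of participant data, actual exposure to the intervention, and post-intervention assessment of the subjects". The intervention runs for one month.
- **Repeated measures analysis of variance (RM-ANOVA).** The method "will be used to investigate the effects of the type of intervention on health variables across three assessment points using SPSS version 22". Mauchly's test is to check sphericity, with degrees of freedom corrected by Greenhouse–Geisser.
- **Sample size.** The calculation addresses "the difference in repeated measures between two independent groups using MANOVA with a power set at 0.80 with medium to high effect size" at alpha 0.05. "The estimated sample size is 128 or 64 participants per senior center group". The effect is given only in words, and the number of repeated measurements is not given.

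**The concern.** The schedule names two measurement occasions and the analysis needs three. This looks like more than a slip in one number, because the rest of the analysis paragraph assumes at least three. With two occasions there is only one difference score, sphericity holds automatically, and both Mauchly's test and the correction are empty.

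This is the only between-group comparison of physical status, cognition and quality of life (Quantitative aim 2). If a third assessment is intended, the centres must know when to collect it, and a missed one cannot be recovered. If it is not intended, the analysis text describes a test that the data will not support. The stated power of 0.80 also depends on the answer, since the number of measurements enters the calculation.

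**Working it through.** **Inputs from the document.** Alpha 0.05, power 0.80, two groups of 64 (N = 128), repeated-measures MANOVA (Sample size). Two assessments (Data collection and timeline). Three assessments (RM-ANOVA section).

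**Assumption.** The effect is stated only as "with medium to high effect size". I take f = 0.25 (conventional medium) as the lower end and f = 0.40 (conventional large) as the upper end.

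**Formula.** For the group-by-time interaction in a repeated-measures MANOVA with two groups and m measurements, power comes from the noncentral F distribution with df1 = m − 1, df2 = N − m and λ = N·f².

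**Step 1: reproduce 128.** With m = 2 and f = 0.25, λ = 128 × 0.0625 = 8, df1 = 1 and df2 = 126. Power is 0.801. N = 126 gives 0.795, so 128 is the smallest equal-group total that reaches 0.80. A two-sample t-test at d = 0.5 has the same noncentrality (0.5² × 64/2 = 8) and the same power, 0.801.

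**Step 2: same formula with m = 3** (df1 = 2, df2 = 125 at N = 128).

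| f | Power at N = 128 | N for power 0.80 |
|---|---|---|
| 0.25 | 0.706 | 158 |
| 0.278 | 0.80 | 128 |
| 0.30 | 0.861 | 111 |
| 0.35 | 0.948 | 82 |
| 0.40 | 0.985 | 64 |

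So 128 also follows from three measurements, at an effect inside the stated verbal range.

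**Step 3: dependence on convention** (f = 0.25, N = 128, three measurements).

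- Univariate RM-ANOVA with λ = 8 under sphericity: 0.712.
- Baseline-to-post group difference held at its two-measurement size, under compound symmetry. If half the effect is present at the middle visit, λ stays at 8 and MANOVA power is 0.71. If the full effect is present at both later visits, λ = 8 × 4/3 = 10.67 and power is 0.83.
- λ = f²·N·(m − 1) = 16: RM-ANOVA power 0.95.
- λ = f²·N·m/(1 − ρ) under sphericity: above 0.99 for ρ from 0 to 0.7.

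**Step 4: a single contrast.** A baseline-to-end contrast with 1 df and λ = 8 has power 0.80 at N = 128, whether or not a middle visit exists.

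**Step 5: baseline adjustment with two assessments.** The 0.80 at a 0.5 SD difference is the unadjusted figure. Adjustment for baseline multiplies the residual variance by 1 − ρ². At ρ = 0.5 (assumed), the standardised difference becomes 0.5/√0.75 = 0.577, λ = 8/0.75 = 10.67, and power is about 0.90.

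**The case against.** The best defence is that Step 2 of the timeline is a condensed narrative and not a visit table. It does not say that there are only two assessments, and an article may leave exact timing to a fuller protocol. Mauchly's test and Greenhouse–Geisser also agree with the three points named in their own section, so they are no separate defect. This stands in part: a third assessment may well exist elsewhere. But the section is headed as the timeline and does give the assessment sequence, and that sequence differs from the one the analysis uses. This is a disagreement between two statements, and not merely an omitted detail.

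A reader might go further and infer that 128 was computed for two measurements, so that the trial has power 0.71 instead of 0.80 once three are analysed. The defence against that reading succeeds. The document never states f = 0.25. An effect of 0.278 with three measurements also gives 128 at 0.80, and over most of the range from 0.25 to 0.40 the three-measurement power meets or exceeds 0.80. The planned test is RM-ANOVA, not MANOVA, and under some noncentrality conventions a third point raises power. The exact match in Step 1 is suggestive, but a plain t-test produces the same number.

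**Conclusion.** The contradiction between two scheduled and three analysed assessments holds on the face of the document, without any assumption, and should be corrected.

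The power consequence is conditional. It reaches 0.71 only for a 2-df interaction at an assumed f = 0.25 with λ = N·f². Under that same formula it runs up to 0.985 at f = 0.40. The documents therefore support neither a claim that the trial is underpowered nor a claim that 128 was miscalculated. They support a narrower conclusion: the stated 0.80 cannot be verified, because the effect is given as a verbal range and the number of measurements is missing from the calculation and inconsistent elsewhere.

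**What to change.** Reconcile Data collection and timeline with the RM-ANOVA section.

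- **If there are two assessments:** remove the reference to three points, Mauchly's test and the Greenhouse–Geisser correction. Use a two-point group comparison, either the group-by-time test or one adjusted for baseline. Quote 0.80 at 0.5 SD as the unadjusted figure; adjustment raises it.
- **If there are three:** place the third assessment in the timeline, name the contrast that carries the conclusion, and restate the power for the test actually used. A 1-df baseline-to-end contrast at the same noncentrality keeps 0.80.
- **In either case:** replace the verbal effect size in Sample size by the number used, and state how many measurements the 128 assumes.

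The cost is wording, and possibly a less favourable stated power if a 2-df interaction at f = 0.25 turns out to be the intended test. No extra participants are needed.
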